### *Individual elements*

Individual-level support for behaviour change delivered to each participant will consist of a face-to-face health coaching session (1–3 days following workstation installation; approximately 30 minutes) and four telephone calls at weeks 2, 4, 8 and 12 (7–10 mins each) following the individual session. Where feasible, the same health coach will remain the point of contact for each participant throughout the study to facilitate rapport. All health coaches will have at least a bachelor’s level training in psychology or a related discipline and will receive training in motivational interviewing techniques adapted for study purposes [53]. Detailed intervention scripts will be used for coach training with accompanying checklists used during intervention delivery to maintain intervention fidelity. Further, health coaches will debrief regularly (monthly for the first few months and then quarterly) via telephone with chief investigators responsible for this element of the intervention (EE, GH) during the active intervention phases.

#### Individual coaching

The coaching will be used to: explain the *Stand Up, Sit Less, Move More* intervention targets; to feedback participant’s assessment results on the extent to which the participant is meeting these targets (derived from the activity monitors worn at baseline; Additional file 4: Figure S4); and, to identify specific goals and behaviour change strategies relating to each of these key intervention messages. The strategies identified in the brainstorming session will be shown to participants who will be encouraged to develop their own strategies as appropriate. A laminated workstation tracker (Additional file 5: Figure S5) will be provided for participants to record their goals and strategies. They will be encouraged to place this within eyesight of their workstation for self-monitoring purposes. Health coaches will record these goals on their own intervention worksheet, which will be referred to during the telephone calls. During this face-to-face session, participants will also receive instruction on the ergonomic setup and appropriate use of the workstation. This will include specific instructions to “listen to their body”, and to regularly change posture (i.e. to neither sit or stand for too long). Following the consultation, a personalised email summary of the session will be sent to participants from the health coach.

#### *Telephone calls*

Four telephone calls will be used to support goal attainment. They will involve assessment of participant progress toward previously set goals, problem-solving as necessary, and adjustment/progression of goals and related behaviour change strategies. The second phone call (week 4) will also address strategies to reduce sitting time outside the workplace. Health coaches will record notes about individual’s progress and amended goals, while participants will be encouraged to update their workstation tracker accordingly. Call attempts, completions, and duration will be tracked, and a call content checklist completed after each call to inform an evaluation of intervention fidelity.

### Data collection

Assessments will be undertaken at baseline, 3-, and 12- months in designated testing rooms at the respective worksites by trained project staff. Participants will receive verbal and written requests (with confirmation of compliance at data collection time) to refrain from any MVPA, alcohol, and caffeine in the 24 hours preceding each assessment, and to fast for at least eight hours. This is to minimise any potential confounding with respect to biomarker outcomes. A fasting blood sample will be collected on-site and the sample analysed by an accredited pathology laboratory. Sitting, standing, and moving time outcomes will be collected via activity monitors in the seven days following the onsite assessment. Participants will receive full instruction on the use of the activity monitors and the accompanying daily log. The devices and the daily logs will be collected by research staff at the end of each seven day period. A self-administered questionnaire will be completed online using the LimeService (http://www.limeservice.com) survey creation and hosting platform. Participants will access the survey using unique tokens contained within an email invitation. This ensures both exclusivity and confidentiality. In addition, descriptive information relating to the respective intervention worksites (e.g.,: office layout and stair availability will be obtained by research staff. Full details of the measures are provided below and in Table 1.

**Table 1 T1:** Summary of measures used in the Stand Up Victoria office workplace intervention

**Behavioural**	**Objectively measured physical activity and sitting time**
*Objective & self-report*	*activPAL3*
	**● Workplace sitting time (primary outcome)**
	**● **Prolonged (>= 30 mins) workplace sitting time
	**● **Workplace standing time
	**● **Workplace moving time (stepping time, no. steps)
	**● **Number of sit-stand transitions at workplace
	**● **Non-workplace sitting, standing, moving time
	*Actigraph GT3X+*
	**● **Average daily MVPA
	**● **Average daily light physical activity
	*Self-report measures*
	**● **% sitting, standing, walking and physically demanding tasks at work
	**● **Recent work attendance (days/week; hours/week)
	**● **Non-workplace sitting time; TV/video viewing time
	**● **Diet (fat intake; fibre intake)
	**● **Smoking status
**Anthropometric***Objectively measured*	**● **Height (baseline only)
	**● **Weight
	**● **BMI (kg/m^2^)
	**● **Waist circumference
	**● **Hip circumference
	**● **Waist-Hip ratio
	**● **Body composition (% and kg fat and fat-free mass)
**Cardio-metabolic***Objectively measured*	**● **Fasting blood glucose
	**● **Fasting insulin
	**● **Cholesterol (total, HDL, LDL)
	**● **Triglycerides
	**● **Blood pressure
**Socio-demographic***Self-report*	All baseline only
	**● **Age
	**● **Gender
	**● **Race/ethnicity
	**● **Marital status
	**● **Education
**Health status** Self-report	**● **History of diabetes & hyperlipidaemia (baseline only)

	**● **Musculoskeletal health
	**● **Eye strain
	**● **Stress-related symptoms (fatigue, headaches, digestive problems, sleep quality)
**Work** Self-report, internal DHS measure, and employee records	**● **Employment status (baseline only) including length of tenure; job classification; full-time equivalent (FTE) level
	**● **Secondary employment status (including FTE)
	**● **Productivity
	**● **Presenteeism/absenteeism
	**● **Work performance
**Psychosocial-Environmental**Self-report and objectively measured	**● **Perceptions of the work environment
	**● **Desk/workstation utilisation
	**● **Frequency and duration of working with colleagues as well as perceived adequacy of space(s) for such interactions.
	**● **Quality of life
	**● **Acceptability of workstations (intervention group only)
	**● **Preference for sitting and standing in the workplace
	**● **Knowledge
	**● **Barrier self efficacy
	Perceived behavioural control
	**● **Perceived organisational social norms
	**● **Use of self-regulation strategies
	**● **Use of intervention-specific strategies
	**● **Descriptive office audit
**Cost-effectiveness**Self-report	**● **Health-related quality of life
	**● **Health care utilisation
	**● **Cost to deliver intervention
	**● **Adverse events (intervention group only; 3 and 12 months only)

All measurements completed at baseline, 3- and 12-months except where noted.

### Outcomes

#### *Sitting, standing and moving time*

Sitting, standing, and moving time will be objectively measured via an activPAL3 activity monitor (PAL Technologies Limited, Glasgow, UK; default settings). This monitor continuously records the precise beginning and ending of each bout of sitting or lying (here termed sitting), standing, and stepping at a variety of speeds, and the estimated MET-hours expended during those bouts. Previous studies have shown this device to be valid, reliable and responsive [54-57]. Waterproofing of the device will be achieved by first inserting it into a nitrile finger cote and then wrapping the device in waterproof *Opsite Flexifix*^
*(™)*
^ (Smith & Nephew).Thereafter, the activPAL3 will be secured to the anterior mid-line of the right thigh, about a third of the way down from the hip, using hypoallergenic adhesive material (*Hypafix®,* BSN medical). Additional hypoallergenic patches will be given to participants for the adhesive materials to be changed as required. Participants will be requested to wear the activPAL3 activity monitor for 24 hours per day, for seven consecutive days at each assessment period (baseline, 3-, and 12-months). At each assessment, participants will also concurrently wear the tri-axial GT3X + Actigraph activity monitor (ActiGraph, Pensacola, Florida). Participants will be asked to wear this activity monitor during waking hours only (except for water-based activities) for the seven-day assessment period. The accelerometer is positioned over the right hip via an elastic belt. The raw accelerometer data will be collected at 30Hz.

Daily logs (self-completed) will be used to record wake and sleep times, work hours (defined as time spent at the primary DHS study worksite), and any device removal greater than 15 minutes. Periods of work time spent not at the primary worksite (i.e. working from home) will also be recorded. A customized SAS 9.3 (SAS Institute Inc., Cary, NC) program, utilising both the activity monitor and log data, will be used to generate sitting, standing, and moving outcomes at work and overall, with the primary outcome being sitting time at work (measured by activPAL3). Consistent with the intervention message, prolonged sitting is defined as time accrued in sitting bouts at least 30 minutes in length. The number of transitions between sitting and standing will also be measured. The GT3X + activity monitor will be used to differentiate time spent in light-intensity physical activity and MVPA.

#### *Anthropometry: height, weight and body composition*

Waist circumference will be measured (nearest 0.1 cm) with a non-expandable tape at the midpoint between the lowest rib and the iliac crest. Hip circumference (nearest 0.1 cm) will be taken as the maximum circumference in the horizontal plane, measured over the buttocks. For both waist and hip measures, measurements will be taken in duplicate with a third measurement taken if the first two differ by ≥ 1 cm. Fat mass, fat-free mass and percent body fat will be measured using foot-to-foot bioelectrical impedance analysis (BIA) scales (Model TISC-330S, Tanita Inc., Tokyo, Japan) in the fasted and voided state. Bioimpedance analysis will not be conducted on participants with a pacemaker. Weight will concurrently be measured using the same BIA scales without shoes and wearing light garments to the nearest 0.1 kg. Standing height will be measured to the nearest 0.1 cm, without shoes and the individual’s eyes looking straight ahead (Frankfort plane), using a portable stadiometer. Height will be measured in duplicate with a third measurement taken if the difference is ≥ 0.5 cm. Body mass-index (BMI; kg/m^2^) will be calculated using the average height and weight obtained from the above measures.

#### *Cardio-metabolic markers*

Fasting blood samples will be collected on-site in the morning by a trained phlebotomist for the analyses of glucose, lipids (triglycerides, high density lipoprotein [HDL] cholesterol and low density lipoprotein [LDL] cholesterol) and insulin. Samples will be sent immediately to an accredited testing laboratory for analysis (Melbourne Pathology). Fasting plasma glucose will be measured by spectrophotometric-hexokinase method. Fasting total cholesterol, HDL- cholesterol and triglycerides will be measured via standard enzymatic-colorimetric methods. LDL-cholesterol will be estimated using the Friedewald equation [51]. Insulin will be measured by electrochemiluminescence immunoassay (ECLIA). All blood chemistry analytes will be measured using Roche/Hitachi cobas® system analysers (Tokyo, Japan). Blood pressure will be measured via a digital blood pressure monitor (OMRON HEM-907; Omron Healthcare, Japan) using the right arm and an appropriately sized cuff. Participants will rest in the seated position for 15 minutes prior to having a minimum of two measurements taken at one-minute intervals. A third measurement will be taken if the systolic differs by >10 mmHg or the diastolic by >6 mmHg.

#### *Survey measures*

**Socio-demographic characteristics** Based on questions used in the Australian Diabetes, Obesity and Lifestyle (AusDiab) study [58], information relating to age, gender, ethnicity, marital status, and education will be obtained (baseline assessment only).

**Physical health history data** Musculoskeletal health will be measured using the 27-item Nordic Musculoskeletal Questionnaire, modified to refer to the last seven days and the last three months (instead of 12 months) [59]. This questionnaire includes items on 'trouble’ in numerous body parts as well as the capacity to perform normal activities in the presence of any 'troubles’, and has been shown to be repeatable and sensitive to change [60]. Eye-strain will be assessed with three items used in a previous ergonomics intervention study, where it was shown to have high internal consistency [61]. A checklist, adapted from previous work that has demonstrated good internal consistency [62], will assess physical health symptoms commonly associated with stress such as fatigue, headaches, digestive problems and sleep quality. Current smoking status (including at work) and history of diabetes and hyperlipidaemia will also be collected.

**Self-reported physical activity and sitting time** Participants will be asked to estimate the total time spent watching TV/videos during the week and on weekends; average daily sitting time during the week and on weekends; and the proportion of sitting, standing, walking and physically demanding tasks during a typical work day in the previous seven days [63,64].

**Work outcomes** Productivity, presenteeism, and absenteeism will be obtained for each assessment period using internal DHS measures and validated questionnaires [65-67]. The Health and Work Questionnaire (HWQ) has six sub-scales (productivity, concentration/focus, supervisor relations, non-work satisfaction, impatience/irritability), with internal consistency scores ranging from alpha = 0.72 to 0.96 [65]. In addition, a total HWQ score will be calculated (alpha = 0.81) [65]. Self-reported work performance will be assessed on a 9-item, 10-point scale [66]. Performance items include amount and quality of work accomplished, meeting deadlines, frequency of errors, taking responsibility, creativity, getting along with others, dependability and overall performance [66]. Presenteeism and absenteeism will be assessed using the proprietary Work Limitations Questionnaire (WLQ), which examines the frequency of difficulty to perform specific job tasks [67].

**Work history and environment** Questions will assess perceptions of the work environment and current work patterns including: length of tenure; job classification; FTE level; desk/workstation utilisation; environmental satisfaction; and, frequency and duration of working with colleagues as well as perceived adequacy of space(s) for such interactions. Previously validated instruments [35,66,68] and items developed specifically for this study (Additional file 6: Figure S6) will be used.

**Dietary intake** will be measured using the 20-item Fat & Fibre Behaviour Index which asked about eating habits over the previous month. This questionnaire has previously been used in our randomised controlled trials and has been shown to be sensitive to change [69].

**Mediators** Potential mediators of change have been conceptualised under the three levels of intervention (organisational, environmental, individual). All mediators will be assessed in both groups at all assessments via the on-line questionnaire. The organisational mediator to be assessed will be the site-specific team champion’s attitudes and knowledge (scales described below). At the environmental level, participants will be asked to report the frequency of use of their workstation in the past month on a 5-point Likert scale (from 'never’ to 'very often’). Individual-level mediators will include the following theoretical constructs: preference for sitting and standing at work; knowledge; barrier self efficacy; perceived behavioural control; perceived organisational social norms; as well as frequency of use of self-regulation strategies and other individual-level intervention strategies. There are no existing measures for these individual-level constructs in relation to workplace sitting; therefore, where possible, we have adapted scales from the more developed physical activity literature or otherwise a study-specific scale was created. All of the scales were pilot tested in our previous workplace sitting intervention [20] and the psychometric properties (internal consistency and test-retest reliability) of these scales can be found in Additional file 7: Table S1. Preference will be measured across two items on a 5-point scale indicating the proportion of work time participants preferred to be sitting or standing (ranging from 'none of the time’ to '80-100% of time’). Knowledge of key intervention messages will be assessed across five items (e.g., “Sitting for most of the time at work is bad for my health”); on a 5-point Likert scale ('strongly disagree to 'strongly agree’). The barrier self efficacy scale has been adapted from an existing scale [70] and will assess nine items referring to specific barriers to reducing workplace sitting (e.g., confidence to 'stand up during meetings at work, even though no one else was’), which will be assessed on a 5-point Likert scale ('not at all confident’ to 'very confident’). Perceived behavioural control will be examined across five items (e.g., 'It is my choice whether I stand up or sit during a meeting with colleagues at work’) on a 5-point Likert scale ('strongly disagree to 'strongly agree’). Organisational social norms will be assessed in eight items (e.g., 'My workplace is committed to supporting staff choices to stand or move more at work’) on a 5-point Likert scale ('strongly disagree to 'strongly agree’). Self-regulation will be examined across 10 items on a 5-point Likert scale ('never’ to 'very often’), adapted from an existing scale for physical activity [71] and will include self-regulation strategies targeted in the intervention (e.g., “recorded my sitting or standing at work in a written record”). In addition, frequency of use of intervention-specific strategies is also assessed across nine items on a 5-point Likert scale ('never’ to 'very often’). The complete set of questions is provided in Additional file 8: Figure S7.

**Moderators** These will be assessed at baseline in both study groups. Potential moderators will be grouped as: demographic (e.g., age, gender, BMI, health status); work-related characteristics (e.g., position, hours worked per week, main work tasks); office environment characteristics assessed as part of the baseline workplace descriptive audit (e.g., office layout); and behavioural characteristics (e.g., MVPA, sitting outside work hours).

**Adverse events** The adverse events that the participant attributes as “study-related” will be collected at each follow-up assessment in the intervention group only. Health care utilisations (number of visits to GPs and allied health care professionals) pertaining to the adverse event (s) will also be measured as part of the economic evaluation (Additional file 9: Figure S8).

**Quality of life** will be measured using the validated Australian Quality of Life Survey (AQoL-8D) which consists of eight separately scored dimensions (Independent Living, Happiness, Mental Health, Coping, Relationships, Self Worth, Pain, Senses) totalling 35 items [72].

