### Economic evaluation

An economic evaluation will be undertaken alongside the trial to determine whether the intervention represents 'value-for-money’ measured against the control group (current practice). It will address issues of both technical efficiency ('how to do it’) through assessment of key design features of the intervention and the associated cost drivers, and allocative efficiency ('what to do’) through the modelling of longer term consequences and cost offsets. In addition to a 'trial-based evaluation’ (costs and outcomes exactly as per the trial), a 'modelled economic evaluation’ will also be undertaken, which extends the target population, time horizon and decision context.

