#### *Incremental cost-effectiveness analyses*

Detailed pathway analysis will be used to specify all activities undertaken as part of the intervention in order to measure costs of associated resource use (e.g. provision and installation of workstations, information sessions, telephone check-ups, weekly emails, adverse events). Unit costs will be drawn from best available sources for the 2012 reference year. In addition to incremental costs of the intervention (measured against the comparator), incremental cost offsets attributable to disease prevention in the long-term will be reported. The cost data will be combined with the behavioural and biomarker outcomes to produce a range of incremental cost effectiveness ratios (ICERs), across both primary and secondary outcomes, including cost per unit reduction in sedentary time and cost per quality-adjusted life year (QALY) gained (based on AQoL-8D [72]). The modelled evaluation will use a Markov approach to estimate the health and cost impacts of changes in sedentary status over the lifetime of participants. Standard discounting will be applied to both costs and outcomes. Simulation-modelling using the @RISK software package will be employed to calculate 95% uncertainty intervals (median, 2.5 and 97.5 percentiles) around the epidemiological probabilities and cost estimates.

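### Adverse events are collected only in the intervention arm and only when the participant attributes them to the study, so adverse event rates have no control reference and the costing of related visits is unclear

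*Protocol article*

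**What the plan says.** Under Survey measures, the adverse events paragraph sets two conditions. The first is the participant's own causal judgement: "The adverse events that the participant attributes as “study-related". The second is the arm: these events "will be collected at each follow-up assessment in the intervention group only". Table 1 agrees, listing under cost-effectiveness "Adverse events (intervention group only; 3 and 12 months only".

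The same paragraph says that GP and allied-health visits "pertaining to the adverse event (s) will also be measured as part of the economic evaluation". No other passage of the text describes how health care use is measured. Table 1, however, has a separate cost-effectiveness entry, "Health care utilisation", with no arm restriction. Its footnote reads "All measurements completed at baseline, 3- and 12-months except where noted". The section on the control condition says that controls have the same assessments as the intervention group at all three time points.

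On costs, the Economic evaluation section says that value for money is "measured against the control group (current practice". The section on incremental cost-effectiveness includes adverse events in its list of costed intervention resources: "telephone check-ups, weekly emails, adverse events".

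**The concern.** Office workers have complaints and see their doctor whether or not they are in a trial. A count of events from one arm, filtered by what the participant blames on the study, mixes effects of the intervention with this background and gives nothing to subtract. The article excludes people with a pre-existing musculoskeletal complaint, so new complaints and injuries are of particular interest, and the workstation stays in place for 12 months.

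The same filter then reaches the economics. If the visits tied to adverse events are the only health care use that is costed, the control arm contributes no visits because nobody asked, not because there were none. Under Intervention messages, one aim of standing up is to reduce musculoskeletal symptoms. Visits avoided for that reason would be a benefit that this data stream cannot show.

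At stake are the between-arm safety statement and the trial-based cost-effectiveness ratios. The primary outcome is not affected.

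**Working it through.** The plan gives no figure on this point, so there is none to reproduce. The check sets the passages side by side and then examines the cost argument.

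**1. What can be compared between arms**

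- Adverse events: intervention arm only, attribution required (Survey measures; Table 1). Not comparable.
- Visits tied to those events: they can exist only where an event was recorded. Not comparable.
- Musculoskeletal symptoms, eye strain and stress-related symptoms (fatigue, headaches, digestive problems, sleep): no arm restriction in Survey measures or Table 1, and the footnote puts them at all three assessments. Comparable.
- All health care use: comparable if the Table 1 entry means all visits in both arms, and not if it means only the adverse-event visits. The article does not say which.

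**2. How far the symptom scales fill the gap**

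The musculoskeletal questionnaire is modified to cover the last seven days and the last three months. At the 3-month visit it covers months 0 to 3. At the 12-month visit it reaches back to month 12 − 3 = 9. Months 3 to 9 are not covered. Injuries or events outside these scales are not asked of controls at any visit.

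**3. When one-arm visit data bias the incremental cost**

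Per person, let b be background visits, f the fraction of background visits wrongly blamed on the study, c visits caused by the intervention, g the fraction of those that are attributed to it, and a visits avoided because of it.

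- True increment: (b − a + c) − b = c − a
- Recorded increment with one-arm collection: g·c + f·(b − a)
- Error = recorded − true = f·b + (1 − f)·a − (1 − g)·c

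The article gives none of these quantities, so the values below are assumptions.

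- No true effect (c = a = 0): the error is f·b. With b = 0.1 and f = 5% it is 0.1 × 0.05 = 0.005 visits per person. With b = 1.0 and f = 20% it is 1.0 × 0.20 = 0.20.
- A true excess of c = 0.1, a = 0 and, as an extreme, none of it attributed (g = 0): the error is 0.005 − 0.1 = −0.095 at the low end and 0.20 − 0.1 = +0.10 at the high end.

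Misattributed background visits and uncredited avoided visits overstate the incremental cost. Caused but unattributed visits understate it. The sign is not fixed.

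**4. What collection in both arms would give**

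From the Sample size section, 160 per arm with 30% attrition leaves 160 × 0.7 = 112. Dividing by the article's design effect for non-activity outcomes gives 112 / 1.19 = 94 effective participants per arm. With assumed event proportions, power at the two-sided 5% level is about 25% for 5% v 10%, 48% for 10% v 20%, 63% for 5% v 15% and 78% for 10% v 25%. The gain would be an estimate by arm with its confidence interval, not a decisive safety test.

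**The case against.** The strongest reply is that the trial does compare the most plausible harms. Pain, eye strain and fatigue are measured in both arms, and the Sample size section gives detectable differences for eye strain and fatigue, so comparison is intended. This stands. A reader might infer from the adverse events paragraph that harm cannot be compared at all; the article does not support that. What remains out of reach is the adverse event rate itself, discrete injuries and other events outside the scales, and musculoskeletal complaints that arise and resolve between months 3 and 9.

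The second reply concerns cost. A reader might infer that the incremental cost is certainly biased. That does not follow either. Table 1 marks adverse events as intervention-only but places no such mark on health care utilisation, so general use may well be collected in both arms, and an unbiased between-arm difference would then be available. The instrument is in an additional file that is not shown. This also stands, but the text describes only the visits tied to adverse events, so the two places need to be reconciled.

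Third, a visit truly caused by the workstation has no control counterpart, so zero is the right comparator for it. In the formula above the error is indeed zero when f = 0, g = 1 and a = 0. That requires participants to attribute perfectly and no visits to be avoided, and nothing in the article secures either condition.

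Finally, asking controls about study-related events would make little sense, since they are told that the study examines the consistency of activity patterns. This is a reason for a neutral question in both arms, not for leaving controls out.

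**Conclusion.** The point holds in a limited form. Adverse event collection is restricted by arm and by participant attribution in explicit text, repeated in Table 1, so a between-arm difference in adverse event rates is not estimable and cannot be repaired at the analysis stage. Symptom outcomes remain comparable.

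The cost limb is conditional. If the adverse-event visits are the only health care use that is costed, the incremental cost carries a bias whose sign is unknown. Its size cannot be derived from the article; the illustrative errors above run from −0.095 to +0.20 visits per person and rest wholly on assumed rates. If Table 1 means all health care use in both arms, this limb falls away once the article says so. The change should be made because it is cheap and must be in place before follow-up data are collected.

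**What to change.** - At 3 and 12 months, ask both arms the same neutral question: any new or worsened health problem or injury since the last assessment, and the GP and allied-health visits for it. Make attribution to study activities a follow-up item, not a condition of entry.
- Report the events by arm, with attributed events as a subset, and use the between-arm difference in visits in the cost-effectiveness analysis.
- Reconcile the adverse events paragraph with Table 1, so that health care utilisation is defined once and collected in both arms.

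The cost is one item block in the online questionnaire that controls already complete, and so a slightly longer control survey. Self-report by participants who know whether they have a workstation can still differ between arms; the change supplies the missing reference rate but does not remove that limitation.
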